### Intervention group: wilderness programme

The development of the WAYA programme affected by cancer has previously been published.^24^ The WAYA programme aims to increase physical activity, self-confidence, self-efficacy and self-care, to support personal growth and building meaningful relationships, and to provide an enjoyable and safe stay in nature. Nature in the WAYA programme has both a contextual and an active role in support of the health and well-being of AYAs affected by cancer, wherein their health is regarded to be intrinsically interwoven in a bidirectional fashion with the health and well-being of nature.^29^ Participants are given the opportunity to experience a diversity of natural landscapes, and specific nature characteristics are actively incorporated in programme activities. Activities in the programme include hiking, sea-kayaking, backpacking, rock climbing and camping. The programme also includes (nature) reflective practices such as mindfulness, meditation and forest bathing.^24^ Outdoor skills taught include mapping/compass/orienting, trail cooking, safety training, equipment planning, foraging, fishing, bush-craft skills and leaving no trace. The wilderness programme consists of three intervention parts: (1) An 8-day intervention that includes 2 days for travelling and physical testing and a 6-day wilderness expedition; (2) A 3-month in-between period where participants are contacted once every month online to coach them to engage in their own outdoor activities and (3) A 4-day intervention including a 2-day base camp programme. Both the expedition and basecamp programme will take place in natural settings around the High Coast of Sweden or in Southern Norway. The group size will be 10–12 participants, and the facilitator–participant ratio will be 3:10. The 6-day wilderness expedition will be logistically supported by a team of 5–7 volunteers.

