#### Safety-related outcomes

An occurrence of (serious) AEs during the interventions is reported and documented in the field diaries. AEs will be coded according to the Medical Dictionary for Regulatory Activities^37^ and analysed using preferred terms and allocation to system organ class. The safety of the programmes will be evaluated by analysing the number, seriousness, intensity and types of AEs that are evaluated to be certain, probable/likely or possibly related to the study programmes. Equal safety between the wilderness programme and hotel stay is defined as no significant differences in the risk of having serious AEs on wilderness versus hotel stay participation.

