### Data analysis

χ^2^ statistics, independent samples t-tests and analysis of variance will be used to calculate group differences in sociodemographic variables and cancer characteristics at baseline. The alpha level will be set to 0.05. The primary analysis will investigate changes in the total scores of the PWS and NRS over time from baseline to 1- year follow-up in the intervention group compared with the control group. Missing data will be imputed by means of multiple imputations or by using full-information maximum likelihood estimation.^41^ The analysis of the primary outcome will be based on a linear mixed-effects model and will be fitted to test intervention effects up to 1 year. Adjustments will be made for age, gender, age at cancer diagnoses and study site. Time, intervention arm, interaction between time and intervention arm, age, gender, age at cancer diagnoses and study site are included as fixed effects, and the participant is included as random effect in the model. Statistical analyses will be on the intention-to-treat principle (all participants who are randomised in the study). As sensitivity analyses, the per-protocol data set will be analysed including only participants who have participated for at least 1 day in the wilderness or hotel stay. Secondary outcomes will also be analysed using linear mixed-effects models.

Categorical data will be presented as frequencies and percentages. For continuous data, the number, mean, SD, median, IQR, minimum and maximum will be calculated. A two-sided p<0.05 will be considered statistically significant.

Safety analyses will be performed on the safety analysis set and include all individuals who had participated in one of the programme interventions for at least 1 day. RR with 95% CI will be calculated to indicate the risk of having an AE adjusted to days of exposure to programme interventions. Pearson’s χ^2^ test will be used to calculate differences in AEs severity between the two study arms. A detailed description of the planned statistical analyses will be provided in the statistical analysis plan, which will be finalised prior to database closure and data analysis. All statistical analyses will be performed by using Stata V.18.0.

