### Ethics and dissemination

Participants are informed both orally and in writing that participation in the WAYA-2 study is voluntary. It is made clear that participation in all study-related activities is voluntary, that they can decline participation in any activity without explanation, and that they can withdraw at any time from the programme without stating a reason. Participants are further informed about the purpose of the study, that data will be handled and later published and presented in a confidential way. Informed consent will be obtained from all participants in writing prior to the start of the study and sent to the researcher responsible for screening and intake (see online supplemental material 1 for an example of the participant consent form). In Norway and Sweden, participants from age 16 can provide individual informed consent without permission/signature from parents/guardians. Participation in the WAYA programme is without costs for participants.

10.1136/bmjopen-2024-087626.supp1Supplementary data

The WAYA-2 study will be performed in line with the instructions and precautions described in the study safety plan.^24^ A physician with emergency medicine expertise will be available by telephone in case of emergency. Adequate insurance for all participants and facilitators in the study will be provided by Mid Sweden University or Agder University. The study protocol was approved by the Swedish Ethical Review Authority on 27 September 2023 (reference: 2023-05247-01). The study application to the Norwegian Ethical Review Authority is pending (reference: 694114). Information letters and consent forms will be accessible on request.

We aim for a wide communication and dissemination of research results through close collaboration with national and international research partners and the wider communities in the respective countries. Results of the study will be presented to the participants. It aims to publish at least three scientific (peer-reviewed) articles and to present the results at (scientific) national and international conferences. Popular articles with study results will be disseminated in the form of interviews, books and chronicles. News items will also be spread via social media (Facebook, Twitter), websites and newsletters of collaborating partners and organisations and of the funding bodies.

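### The safety set requires at least 1 day of participation, a condition that an adverse event can itself prevent; the effect is small and removing it is free

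*Protocol article*

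**What the plan says.** All references are to the protocol article.

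- **Safety set (Data analysis).** The safety analyses "include all individuals who had participated in one of the programme interventions for at least 1 day". The text does not say whether a day means a calendar day, any part of one, or 24 hours.
- **Estimator (Data analysis).** "RR with 95% CI will be calculated to indicate the risk of having an AE adjusted to days of exposure to programme interventions".
- **Recording of events (Safety-related outcomes).** "An occurrence of (serious) AEs during the interventions is reported and documented in the field diaries". No minimum stay is attached.
- **Safety criterion (Safety-related outcomes).** Equal safety means "no significant differences in the risk of having serious AEs on wilderness versus hotel stay participation".
- **Content of the first stay.** The wilderness arm has "An 8-day intervention that includes 2 days for travelling and physical testing and a 6-day wilderness expedition". The section on the hotel stay gives the control arm the same two days for travel and testing. Table 1 puts the VO2max, blood pressure and heart rate measurements on day 1; its footnote moves only the self-reported questionnaires to another date.
- **Leaving early (Ethics and dissemination).** Participants are told that "they can withdraw at any time from the programme without stating a reason".
- **Per-protocol set (Data analysis).** The same threshold is used for the sensitivity analysis, "including only participants who have participated for at least 1 day in the wilderness or hotel stay".

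**The concern.** A safety population should be fixed by exposure having begun. Here it is fixed by how long exposure lasted, and an AE can determine that. Someone injured or taken ill within hours of starting, who then leaves, may fail the 1-day condition because of the event. The person leaves the denominator and the event leaves the numerator. The events exposed to this are those serious enough to end participation at once, which bear most directly on a criterion based on serious AEs.

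The recording rule and the analysis rule therefore do not match: the field diaries would hold an event that the analysis set may exclude. A 1-day minimum can be reasonable for a per-protocol efficacy analysis. In a safety set it selects on the outcome. What is at stake is the accuracy of the reported AE and serious-AE counts and risks.

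**Working it through.** **1. How many start.** The Sample size section gives 75 per arm, 34.5% attrition before the intervention and 10% during it. As a check on those inputs, a simple two-sample calculation (SMD 0.60, two-sided alpha 0.05, power 80%) needs 44 per arm, and 44 / (1 − 0.345) / (1 − 0.10) = 74.6, which rounds up to the stated 75. This approximates the mixed model that the protocol names. Expected starters per arm: 75 × (1 − 0.345) = 49.1, taken as 49. The upper bound, with no loss before the start, is 75.

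**2. Who can be lost, by meaning of the rule.**

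| Meaning of at least 1 day | Starters who can drop out of the safety set |
|---|---|
| Any attendance on calendar day 1 counts | None |
| A full day is needed; travel and testing days count | Those who leave on day 1, for example after an event in travel or testing |
| A full day is needed; only expedition or hotel days count | Also those who leave on the first expedition or hotel day |

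The rule asks for a day in one of the interventions. A first-day leaver who returned for the second stay would therefore qualify then, and an event on day 1 of the second stay does not remove anyone who completed a day of the first.

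**3. Effect on the reported risk.** Suppose the only serious AE in an arm falls on a first-day leaver. Exact (Clopper-Pearson) 95% limits are used; for zero events in n the upper limit is 1 − 0.025^(1/n).

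| Starters | Person kept | Person dropped |
|---|---|---|
| 49 | 1/49 = 2.0% (0.05% to 10.9%) | 0/48 = 0% (upper limit 1 − 0.025^(1/48) = 7.4%) |
| 75 | 1/75 = 1.3% (0.03% to 7.2%) | 0/74 = 0% (upper limit 1 − 0.025^(1/74) = 4.9%) |

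**4. Effect on the between-arm comparison.** The article does not name a test for serious-AE risk, so two are shown, with no serious AEs in the hotel arm and 49 starters per arm.

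- *One event.* 1/49 against 0/49 gives Fisher p = 1.0 (uncorrected Pearson p about 0.31). After the drop, 0/48 against 0/49 shows no difference. The conclusion is the same.
- *Fisher threshold.* 5/49 against 0/49 gives p = 0.056 and 6/49 against 0/49 gives p = 0.027. Dropping one of the six leaves 5/48 against 0/49, again p = 0.027.
- *Uncorrected Pearson threshold.* For a events against none, with arm sizes m and n and N = m + n, χ² = N(a·n)² / [m·n·a·(N − a)] = N·a·n / [m(N − a)]. For 4/49 against 0/49: 98 × 4 × 49 / (49 × 94) = 4.17, p = 0.041. For 3/48 against 0/49: 97 × 3 × 49 / (48 × 94) = 3.16, p = 0.075. Here one lost event does change the result, but only at the boundary.

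**5. Effect on exposure.** The two stays total 8 + 4 = 12 days. With 49 starters, of whom one stays half a day (assumed), person-days are 48 × 12 + 0.5 = 576.5. The half day is 0.5 / 576.5 = 0.09% of the total. With 75 starters it is 0.5 / 888.5 = 0.06%. Keeping the early leaver changes the denominator of the exposure-adjusted rate hardly at all, while the event is retained.

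**The case against.** The strongest reply is that the phrase is undefined and the protocol counts in whole programme days (day 1, day 8, 8-day and 4-day stays). If attending day 1 is one day, nobody who starts is lost, and day counting is detail that an analysis plan may settle. This stands as a limit: the problem exists only under the stricter meanings. It does not dispose of the point, because the article states a minimum duration as an inclusion rule and its literal wording permits those meanings.

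A reader might also infer that the rule favours the wilderness arm, since leaving after an injury seems more likely on an expedition than in a hotel. The document does not support that. Both arms have the same travel and testing days and nothing quantifies early leaving by arm. A dropped hotel-arm event would make the wilderness programme look worse by comparison.

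A reader might further infer that single events decide the equal-safety conclusion. For the planned comparison they do not, as step 4 shows; one event matters only at the significance boundary.

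Finally, the scenario is uncommon on the document's own evidence: the Introduction reports that none of the 42 pilot participants dropped out and that all pilot AEs were non-serious. The event would also stay in the field diaries, so it would be lost from the analysis and not from the record. Both points stand and keep the size small.

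**Conclusion.** The concern holds in a limited form. The safety set depends on a duration after the start that an AE can cut short, and the recording rule has no matching minimum. Unless any day-1 attendance counts as a day, a first-day leaver is dropped together with the event. The consequence falls on the reported AE and serious-AE counts and risks, for example 2.0% becoming 0% in an arm of 49. An effect on the equal-safety conclusion is not shown and would be rare, and a difference between arms is not documented.

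This rests on three assumptions: 49 starters per arm (75 at most), a serious AE on the first day followed by departure with no return for the second stay, and a strict meaning of the 1-day rule. The document gives no probability for the second. The point is a free improvement to the analysis-set definition and not a threat to the trial's validity.

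**What to change.** In the Data analysis section, or in the statistical analysis plan before database closure, define the safety set as all participants who began any part of a programme intervention, including travel and physical testing, with no minimum duration. Count part days as exposure in the relative risk; that analysis is already adjusted for days of exposure, so short stays need no separate rule. Keep the 1-day threshold for the per-protocol set only, and say there what counts as a day.

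The cost is one or two sentences. It needs no new data, no change in sample size and no change to the conduct of the programmes.

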### Protocol amendments

Possible changes to this protocol, and reasons for these changes, will be documented in the trial register (www.isrctn.com), and if needed submitted to the Swedish and Norwegian Ethical Review Authority for approval. The registered study protocol (ISRCTN93856392) includes all items on the minimum standard checklist of items of the WHO.^42^

### Patient and public involvement

User involvement and collaboration with the wider community were established during our previous WAYA-1 study and will be continued in this study. Three AYAs affected by cancer are on the advisory board of the WAYA-2 study. For all wilderness and hotel stay interventions, at least one member of the facilitating team will be an AYA affected by cancer. The WAYA-2 study design and recruitment strategies have been developed in close collaboration with AYAs affected by cancer, the Swedish cancer organisations for childhood and young cancer, researchers from four different countries (Netherlands, Norway, Sweden, USA) and healthcare professionals from the region Västernorrland in Sweden. The content of the WAYA-2 programme and hotel stay has been developed in close collaboration with the Swedish survival guilt, other outdoor instructors/nature guides and the Swedish cancer organisation and optimised through feedback from previous participants in the WAYA-1 study. All parties as mentioned above will be involved in interpretation and dissemination of study results.

### Ethics and dissemination

Participants are informed both orally and in writing that participation in the WAYA-2 study is voluntary. It is made clear that participation in all study-related activities is voluntary, that they can decline participation in any activity without explanation, and that they can withdraw at any time from the programme without stating a reason. Participants are further informed about the purpose of the study, that data will be handled and later published and presented in a confidential way. Informed consent will be obtained from all participants in writing prior to the start of the study and sent to the researcher responsible for screening and intake (see online supplemental material 1 for an example of the participant consent form). In Norway and Sweden, participants from age 16 can provide individual informed consent without permission/signature from parents/guardians. Participation in the WAYA programme is without costs for participants.

10.1136/bmjopen-2024-087626.supp1Supplementary data

The WAYA-2 study will be performed in line with the instructions and precautions described in the study safety plan.^24^ A physician with emergency medicine expertise will be available by telephone in case of emergency. Adequate insurance for all participants and facilitators in the study will be provided by Mid Sweden University or Agder University. The study protocol was approved by the Swedish Ethical Review Authority on 27 September 2023 (reference: 2023-05247-01). The study application to the Norwegian Ethical Review Authority is pending (reference: 694114). Information letters and consent forms will be accessible on request.

We aim for a wide communication and dissemination of research results through close collaboration with national and international research partners and the wider communities in the respective countries. Results of the study will be presented to the participants. It aims to publish at least three scientific (peer-reviewed) articles and to present the results at (scientific) national and international conferences. Popular articles with study results will be disseminated in the form of interviews, books and chronicles. News items will also be spread via social media (Facebook, Twitter), websites and newsletters of collaborating partners and organisations and of the funding bodies.

### Timeline of the study

The timeline of the study is depicted in figure 1. The first participants were enrolled in the study on 19 February 2024. The first interventions in Sweden will be carried out during the summer of 2024. The interventions in Norway will take place in the summer of 2025. Since participants are followed for 1 year after the start of the intervention, data collection will end in July 2026. Data analyses are planned to start in December 2026 and reporting is planned to end in December 2027. It is the aim of this study that participants will be followed up for 10 years after the study starts (2, 5 and 10 years follow-up) to investigate possible long-term changes in psychological well-being, health-related quality of life and physical activity. Ethical approval and finance for the long-term follow-up of the WAYA-2 study will be sought in 2025.

**Figure 1 F1:**

Time line of the WAYA-2 study. WAYA-2, Wilderness Programme for Adolescents and Young Adults.

## Discussion

AYAs affected by cancer are an understudied and vulnerable group and effective interventions are needed to ensure that they are able to cope with late effects of cancer, its treatment and achieve good quality of life. To the best of our knowledge, worldwide this study will be the first full-scale RCT that investigates the effectiveness of a WAYAs affected by cancer, and the first wilderness programme in Scandinavia that is developed and adapted to their needs. The WAYA programme in this study is specifically designed to offer a supervised wilderness programme to AYAs with a wide range of disabilities.^24^

This study aims to demonstrate the evidence base for a wilderness programme intending to impact the psychological well-being of AYAs affected by cancer. The expected short-term impact is that the wilderness programme may support their self-efficacy, self-confidence and provide them with the competence to develop and maintain their own outdoor practice. The long-term impact of the wilderness programme may decrease depression, anxiety, and stress, and increase quality of life. In the development of the previous pilot RCT design, considerable effort was invested to define an appropriate control group activity.^21^ A hotel stay was chosen to control for attention from facilitators, group support and being away from their home environment. Although it might be expected that relaxation and connecting with other AYAs offer positive experiences and time to recharge, it is expected that these may have less impact on their health and well-being in the long term.^43 44^ Based on previous experiences with the feasibility of a planned RCT in Norway,^45^ it was decided not to include a ‘care as usual’ or wait-list control arm in the WAYA-2 study.

This study is expected to fill a gap in the literature by providing valuable insights and needed evidence on the role of nature in the support of the health and well-being of such a vulnerable and understudied population. This will inform AYAs affected by cancer, their families, outdoor instructors, clinicians and other researchers.

One of the expected challenges of this study is to recruit the needed number of participants in the study within the set time frame. We previously published that the eligibility (87.3%) and enrolment rate (95.2%) of participants in the WAYA-1 study were high.^25^ To randomise 150 eligible individuals into the WAYA-2 study, we, therefore, need to recruit at least 180 AYAs affected by cancer to register their interest to participate in the WAYA-2 study. In our previous pilot study, we only recruited among members of Swedish cancer organisations Ung Cancer and the Childhood Cancer Fund, and the recruitment rate was low (3.6%).^25^ However, the pilot study was performed during the COVID-19 pandemic where recommendations with respect to travel restrictions were in place. It is, therefore, expected a higher recruitment rate in the WAYA-2 study. Furthermore, we will now also recruit participants in Norway and additional recruitment strategies will be developed with the support of healthcare professionals and brochures in waiting rooms of oncology departments of hospitals in Norway and Sweden.

Another potential challenge of the WAYA-2 study is the inclusion of a heterogeneous study population (all cancer diagnosis and all cancer treatment stages) with a wide age range (16–39 years). Programme activities and study outcomes may be affected by participants being at very different stages of their cancer trajectory and/or lives. The inclusion of participants with a large span was investigated in detail in the previous pilot study and results have been published.^24^ It appeared that the wide age range and different stages in the cancer process were perceived to be an advantage (rather than a disadvantage) since it positively influenced group bonding and learning process, according to facilitators and participants.

This study involves a unique cross-sectional international (Norway, Sweden, USA) and multidisciplinary collaboration between academic researchers, clinicians, outdoor instructors, public health professionals, patient organisations and non-profit organisations in the outdoor sector. Members of the research team have expertise in clinical trials, epidemiology, nature-based therapies, nursing, oncology, psycho-oncology, public health, social sciences, sport sciences, wilderness therapy and have previously published on the topic.^20 21 24–26 45–49^ It is expected that such a collaboration is needed to tackle the complexity of this multicomponent intervention for AYAs affected by cancer.

